#### Randomization, allocation and concealment

The roles involved in the implementation of the study in each sub-center included PI, data platform manager, participant, community manager (research team), community partner, multidimensional intervention implementation team, health education implementation team, cognitive assessment team, and radiology testing team. A computer generator randomizer method (PI execution) is used to determine the intervention content in each community, and PI is responsible for conducting specific research work in each sub-center. This study could not achieve a perfect “blinding” because the participants are able to clearly perceive the intervention, but we tried to maximize the “isolation” of the intervention/control implementation team in each group to reduce the interaction between the groups.

The intervention/control settings of the three communities in each sub-center are assigned by the platform manager using the computer generator randomizer method to achieve the randomization process in our study.

The PI organizes and contacts all research processes independently, and the data platform manager is not involved in the community effort. All participants in the same community received the same intervention, and subjects in different communities were unaware of each other’s existence. The PI assigns all the research work for their respective communities to three permanent community managers who do not know each other and do not collaborate with the investigator. Community partners are only responsible for research projects in their communities. There is no overlap between the multidimensional intervention and health education teams because they are only responsible for the research in their communities. The cognitive assessment team is primarily composed of temporarily recruited medical students. The team receives homogeneity training from the PI and data platform manager on the use of standards of the cognitive assessment tools and how to use the online platform. The functional MRI test technician of the radiology team only knows the participants` code number and does not participate in any community intervention work except the functional MRI test. The test data file is labeled as “ID + test time”, and PI will retain all data. All cognition-related assessments are collected paperlessly, and community on-site assessment data are directly transmitted to the online research platform (link address: https://ncrcg-brainhealth-1301126429.file.myqcloud.com) to ensure fast and direct data transmission, reducing intermediate transmission processes, and ultimately reduce the risk of contamination.

### Outcomes

Using the gold standard scale as the primary outcomes, the effect of intervention can be evaluated scientifically. At the same time, exercise ability, sleep, nutrition, anxiety, depression and biological indicators are also closely related to cognitive dysfunction, and imaging indicators will be considered as secondary outcomes of this study.

#### Primary outcomes

Cognitive function: The assessment methods included the Montreal Cognitive Assessment (MoCA) Scale, the Subjective Cognitive Decline (SCD-Q9) Scale, the Auditory verb learn test-Huashan version (AVLT-H) Scale, the Shape Trails Test (STT-A/B) Scale, the Animal Fluency Test (AFT) Scale, the Boston Naming Test (BNT) Scale, and the Self-Consciousness Scale (SCS).Magnetic Resonance Imaging (MRI): T1, T2, T2flair, Diffusion Weighted Imaging (DWI), Blood Oxygenation Level Dependent (BOLD), and Diffusion Tensor Imaging (DTI).

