#### Inclusion criteria

The participants were community residents aged 50 and above (age is subject to ID card).The chief complaint of forgetfulness (self-reported memory deterioration in the last five years) or memory deterioration confirmed by a researcher.The baseline Montreal Cognitive Assessment (MoCA) score of less than 26/30 are used primarily to include subjects with cognitive dysfunction; Mini-mental Status Examination (MMSE) scores greater than 22 are primarily used to include subjects with non-severe dementia [24].On the daily instrumental activity scale, Lawton and Brody scored more than 6/8.Being able to live in their own homes rather than hospitals or long-term care facilities.Can read and write by themselves.Do not take anti-dementia medications (e.g., donepezil, galantamine) recently or during the study period.Sign the informed consent form, confirming that you have been informed of all relevant contents of the trial.Able to walk four meters independently with or without a walker.Physical Activity Readiness Questionnaire (PAR-Q) scale confirmed that the participants were healthy enough to participate in the relevant exercise.By utilizing the multi-nutritional assessment short form (MNA-SF) questionnaire to assess nutritional status and also understanding the subject’s history of food allergies, clinical nutrition experts evaluate if they are eligible for nutritional intervention.The Pittsburgh Sleep Quality Index (PSQI) showed no serious sleep disorder.Previous medical history investigations indicate no serious mental illness and no current psychological or psychiatric treatment.Complete all assessment contents and sign the informed consent form.

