#### Health education intervention group

Community on-site group teaching are used for the health education part of the present study, which covered 24 learning topics (Frequency & form: 1 h each time, once a week for 6 months, fixed time and place) such as scientific exercise, joint pain, healthy sleep, nutritious diet, hypertension, diabetes, cognitive disorders, diseases, and new therapies for older adults. The project team will prepare the paper publicity materials based on the theme of each lecture and distribute the health education materials before each lecture. More than ten doctors were organized to conduct a six-month offline health education intervention course for the target participants in the pilot trial of our study.

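### SCD-Q9 and the Self-Consciousness Scale rank as primary cognitive outcomes although participants know what they receive, and the assessment table lists neither

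*Protocol article*

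**What the plan says.** The Outcomes section of the protocol article justifies its choice in one sentence: "Using the gold standard scale as the primary outcomes, the effect of intervention can be evaluated scientifically". Primary outcomes then gives one list under cognitive function. It opens with "the Montreal Cognitive Assessment (MoCA) Scale, the Subjective Cognitive Decline (SCD-Q9) Scale", continues with AVLT-H, STT-A/B and AFT, and ends with "the Boston Naming Test (BNT) Scale, and the Self-Consciousness Scale (SCS"). MRI sequences follow as a second primary item. The list states no order of importance and does not separate what participants report from what they are tested on.

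On masking, the section Randomization, allocation and concealment says: "This study could not achieve a perfect “blinding” because the participants are able to clearly perceive the intervention". It adds that participants in different communities do not know of one another.

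Explanation for choice of comparators names the non-contact group as the control. That group has enrolment and exit assessments, greetings and gifts. Table 1 gives health education to both other groups, and its topics include "nutritious diet, hypertension, diabetes, cognitive disorders, diseases, and new therapies for older adults".

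Table 4, the list of enrolment and exit assessments, contains neither SCD-Q9 nor SCS.

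**The concern.** A self-rating of memory records the participant's own judgement. Someone who knows that they are in a six-month brain-health programme, and who is encouraged and taught about cognitive disorders, may judge their memory differently with no change in what they can remember. Masking the assessor does not help, because the participant supplies the rating.

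SCS adds a question of construct. As named it concerns self-consciousness, and the protocol does not say why that belongs under cognitive function.

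At stake is what a primary result would mean. With these two scales level with MoCA and the memory, trail, fluency and naming tests, a group difference in self-judgement could be reported as a primary effect on cognition. The direction of bias is not certain either: reassurance may lower complaint, while teaching about cognitive disorders may raise it.

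**Working it through.** The protocol gives no figure to reproduce on this point. The check sets its sections side by side.

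**1. The two instrument lists**

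| Instrument | Primary outcomes | Table 4 | Type, by its name |
|---|---|---|---|
| MoCA | yes | yes | performance test |
| AVLT-H | yes | yes | performance test |
| STT | yes | yes | performance test |
| AFT | yes | yes | performance test |
| BNT | yes | yes (BNT-30) | performance test |
| SCD-Q9 | yes | no | subjective rating |
| SCS | yes | no | self-consciousness |
| MMSE | no | yes | performance test |
| DSST | no | yes | performance test |

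Seven cognitive instruments are primary; five of them are in Table 4 and two are not (2/7 = 28.6%). This counts instruments and is not an effect size. It leaves out MRI, which is also primary. The two missing from Table 4 are the same two whose names do not denote a performance test.

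**2. Who supplies the answer**

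Quality control, Data acquisition, has trained assessors administer questionnaires on site. It requires residents to answer for themselves, with no help from relatives. An assessor reading the items aloud does not change whose judgement is recorded. For SCD-Q9 this follows from the scale's name. For SCS it holds only if the scale is self-rated, because the protocol does not describe its items, scoring or administration.

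**3. Scheduled contact by group (Interventions section)**

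- Multidomain: exercise three times a week for about 60 minutes, each session followed by 15–20 minutes of meditation. That is 3 × (60 + 15) = 225 to 3 × (60 + 20) = 240 minutes a week, before sleep and diet sessions and before health education.
- Health education: one 60-minute session a week.
- Non-contact control: no scheduled sessions.

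Minutes do not measure bias. They show only that participants can tell what they receive and that attention differs by group.

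**4. What each contrast carries**

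- Multidomain versus non-contact: awareness of an active programme, encouragement, peer discussion and teaching all differ.
- Health education versus non-contact: attention and teaching about cognition differ.
- Multidomain versus health education: both groups know they are in a programme and both are taught about cognition. The gap is smaller but not zero, because contact still differs (225–240 against 60 minutes a week, leaving aside any lectures the multidomain group also attends).

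**5. Size**

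The protocol gives no expected effect, standard deviation or reliability for either scale, and no estimate of response bias. No magnitude can be computed without inventing the input.

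**The case against.** The strongest reply has four parts.

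- **Combination of outcomes.** The article states no rule by which one positive scale makes the trial a success, and such a rule may sit in an analysis plan that is not shown. A reader might infer that SCD-Q9 alone could win the trial; the document does not say so. What stands is that the protocol itself fixes which instruments are primary, so a difference on either scale can be called a primary result whatever the combination rule.
- **Controls already in the design.** The health education group partly controls for contact and teaching, and participants do not know of the other communities. Both points are fair and narrow the concern. Neither hides from participants what they themselves receive, and the named control remains the non-contact group.
- **SCS is judged by its name.** This is correct, and the statement about SCS must stay conditional.
- **Neither scale may be collected.** If Table 4 is complete, no bias arises from them. The primary list then names outcomes that are not measured, which also needs correction.

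A reader might also infer that enrolment on "self-reported memory deterioration in the last five years" makes complaint scores fall at retest and so manufactures an effect. The document does not support this. The same criterion also admits people whose deterioration a researcher confirms, so complaint is not required of everyone. Any regression to the mean would affect all three groups alike and would not by itself create a difference between them.

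Performance tests can also respond to motivation, but they are less directly exposed than a self-rating.

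**Conclusion.** The concern holds in a limited form. SCD-Q9 should not be a primary cognitive outcome in a trial whose participants know their intervention and whose named control has almost no contact. SCS does not belong there on the evidence of its name, and it carries the same exposure if it is self-rated. The concern is strongest for contrasts with the non-contact control and smaller for multidomain versus health education.

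It affects two of the seven primary cognitive instruments and leaves the five performance tests in place. The size of any bias cannot be derived from the document, and a specific shift in standard deviations would be an assumption. The conclusion rests on reading both scales by their names and on the protocol's own statement about blinding. Separately, the Primary outcomes section and Table 4 disagree on whether the two scales are collected.

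**What to change.** Restrict the cognitive part of Primary outcomes to the performance-based tests that also stand in Table 4: MoCA, AVLT-H, STT, AFT and BNT. Move SCD-Q9 to the secondary outcomes as a patient-reported measure, labelled as open to expectation bias and not as evidence of improved cognition. If it is to be collected, add it to Table 4. Make SCS exploratory, with a stated reason and mode of administration, or drop it. Primary outcomes, Secondary outcomes and Table 4 should then agree.

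The cost is outcome-list wording, plus a registry update if the registration, not seen here, carries the same list. Keeping SCD-Q9 may add one short questionnaire to the existing enrolment and exit assessments. The small downside is that subjective complaint can no longer carry a primary claim.

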### Explanation for choice of comparators

The main aim of this study is to evaluate the effectiveness of multidomain cognitive intervention. Subjects in the non-contact control group (without any intervention) will be selected as the control group to compare the effect evaluation of different intervention intensification (multi-domain collaborative intervention and traditional health education).

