## Methods

### Trial design and study setting

The present study was designed as a multicenter, national, community-based RCT (2020–2024). We followed the Standard Protocol Items: Recommendations for Interventional Trials guidelines (SPIRIT 2013) in developing this protocol.

This program was led by the West China Hospital of Sichuan University (WCHSCU). We advertised for research partners on the National Clinical Research Center for Geriatrics (NCRCG) platform, and 27 hospitals responded. After one-on-one communication, we decided that the project would be carried out simultaneously with 12 sub-center research partners in 10 major Chinese cities. The present study will be conducted in Chengdu City (WCHSCU, Chengdu Fifth People’s Hospital, and The First Veterans hospital of Sichuan Province), Daqing City (Daqing Long Nan Hospital), Nanning City (The First People’s Hospital of Nanning), Hangzhou City (The First Affiliated Hospital, Zhejiang University School of Medicine), Lanzhou City (The First Hospital of Lanzhou University), Nanjing City (Jiangsu Province Geriatric Hospital), Yibin City (The Second People’s Hospital of Yibin), Changchun City (Jilin Provincial People’s Hospital), Qingdao City (Qingdao Municipal Hospital), Tai’an City (Taian City Central Hospital). The signing of study cooperation agreements between WCHSCU and each sub-center and ethical application in each sub-center is in progress. As of May 2023, eight of the 12 sub-centers had completed ethical applications and signed research cooperation agreements, while the remaining four partners are still in the process.

In each sub-center city, three communities are selected: the non-contact control group, the health education group, and the multidimensional intervention group. According to the eligibility criteria, 30 participants from each community were selected to participate in the study. All participants from the same community will receive the same intervention, and all participants will participate in the study for a period of six months, the difference is that participants in different communities receive different interventions.

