#### Secondary outcomes

Physical function: It primarily includes sarcopenia (muscle mass, muscle strength, and physical function), the Fried Scale, and International Physical Activity Questionnaire Short Form (IPAQ-SF).Sleep: Pittsburgh Sleep Quality Index (PSQI).Nutritional status: the multi-nutritional assessment short form (MNA-SF) and body mass index (BMI).Mood disorders: Patient Health Questionnaire-9 (PHQ-9) Scale, and the Generalized Anxiety Disorder-7 (GAD-7) Scale.The plasticity of multidimensional intervention on cognitive impairment biomarkers: The influence of the multidimensional intervention on cognitive impairment biomarkers was studied by micro-protein post-translational modification, metalomics, metabolomics, transcriptomics, and other technologies and compared with AD molecular markers to determine their relationship with disease severity and outcome. To explore the effects of the multidimensional intervention on brain perfusion, iron content, β-amyloid protein, Tau protein and phosphorylated Tau protein, deacetylase 1, IL-6, IGF-1, nitric oxide, platelet, ubiquitin, C-reactive protein, hemocysteine, and other key indicators, quantitative susceptibility mapping (QSM), structural MRI imaging, fluid attenuated inversion recovery (FLAIR) sequence, amyloid and tau PET were used.

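### The protocol contradicts itself on which outcomes are primary, so no outcome or contrast is fixed as confirmatory across the three arms

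*Protocol article*

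**What the plan says.** All references are to the protocol article.

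- **Outcomes (opening paragraph).** On the primary side: "Using the gold standard scale as the primary outcomes, the effect of intervention can be evaluated scientifically". The scale is singular and not named. On imaging: "imaging indicators will be considered as secondary outcomes of this study".
- **Primary outcomes.** Two entries. The first begins "Cognitive function: The assessment methods included the Montreal Cognitive Assessment (MoCA) Scale, the Subjective Cognitive Decline (SCD-Q9) Scale" and goes on to AVLT-H, STT-A/B, AFT, BNT and SCS, seven instruments in all and none ranked. The second is "Magnetic Resonance Imaging (MRI): T1, T2, T2flair, Diffusion Weighted Imaging (DWI), Blood Oxygenation Level Dependent (BOLD), and Diffusion Tensor Imaging (DTI". No measure derived from any of these sequences is named.
- **Secondary outcomes.** Imaging appears again: "quantitative susceptibility mapping (QSM), structural MRI imaging, fluid attenuated inversion recovery (FLAIR) sequence, amyloid and tau PET were used".
- **Table 4 (enrollment and exit evaluation).** The cognitive entries are MoCA, MMSE, DSST, AVLT-H, STT, AFT and BNT-30. The six MRI sequences are also listed. SCD-Q9 and SCS are not.
- **Arms and contrasts.** In each sub-center city "three communities are selected: the non-contact control group, the health education group, and the multidimensional intervention group". Explanation for choice of comparators gives the effectiveness of the multidomain intervention as the main aim and uses the non-contact arm as control "to compare the effect evaluation of different intervention intensification (multi-domain collaborative intervention and traditional health education". It does not rank the contrasts.
- **Statistical methods.** Analysis of variance, covariance and a linear mixed model are planned for comparisons between groups, with the primary responses in the plural.

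**The concern.** Four adjoining parts of one document disagree on what the trial's main question is. Imaging is secondary, then primary, then partly secondary again. The primary scale is one in the Outcomes paragraph and seven in the list beneath it, and two of those seven are missing from the list of assessments at entry and exit. The MRI entries say how images are acquired, not what will be compared, so they cannot be tested as they stand.

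With three arms and no lead contrast, a reader cannot tell beforehand which result will decide whether the multidomain program worked. The scale, the contrast and the rank of imaging could all be settled after results are known. A nominally significant finding on one scale in one contrast could then be presented as the primary result, and nothing in the document would show otherwise.

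**Working it through.** **Step 1. Set the sections side by side.**

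| Item | Outcomes paragraph | Primary outcomes | Secondary outcomes | Table 4 |
|---|---|---|---|---|
| Imaging | secondary | six MRI sequences | QSM, structural MRI, FLAIR, PET | the same six sequences |
| FLAIR | secondary (as imaging) | primary (as T2flair) | secondary | listed |
| Cognitive scales | one, unnamed | seven, unranked | none | five of the seven, plus MMSE and DSST |
| SCD-Q9, SCS | not named | primary | not named | not listed |

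The five primary scales that Table 4 lists are MoCA, AVLT-H, STT, AFT and BNT.

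**Step 2. Does the sample size reveal the confirmatory outcome?** The arithmetic 12 × 90 = 1080 is right. The inputs in Sample size and groups are an MCI prevalence of 0.34, power 0.95 and dropout 0.2. None is tied to a listed outcome, and no alpha or effect size is given, so the sample size does not settle the matter. The protocol states no familywise error rate that could be reproduced.

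**Step 3. Size of the problem under stated assumptions.** Inputs from the document: seven scales, or the five in Table 4, and three arms. Assumed, because the document gives none of it: two-sided 5% per test, no adjustment, any single win counted as success, equal pairwise correlation ρ between scales from 0 to 0.7, and each single test holding its own 5% level. MRI is left out because the document names no imaging endpoint to count.

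One contrast, independent scales:
- Seven: 1 − 0.95^7 = 0.302
- Five: 1 − 0.95^5 = 0.226

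Two contrasts against the non-contact arm, independent scales. For one scale, sharing the control arm gives about 0.091 rather than 1 − 0.95² = 0.0975. Then:
- Seven: 1 − (1 − 0.091)^7 ≈ 0.49
- Five: 1 − (1 − 0.091)^5 ≈ 0.38

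For correlated scales, simulate arm-level standardized means x = √ρ·S + √(1 − ρ)·e. S is common to all scales within an arm, e is specific to the scale, and each contrast is z = (x₁ − x₂)/√2, called significant if |z| > 1.96. At least 200,000 draws were used per cell.

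| Scales | ρ | One contrast | Two contrasts vs non-contact |
|---|---|---|---|
| 7 | 0 | 30% | 49% |
| 7 | 0.3 | 27% | 44% |
| 7 | 0.5 | 23% | 38% |
| 7 | 0.7 | 18% | 30% |
| 5 | 0 | 23% | 38% |
| 5 | 0.3 | 21% | 35% |
| 5 | 0.5 | 18% | 31% |
| 5 | 0.7 | 15% | 26% |
| 1 | – | 5% | 9% |

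One three-group test per scale, as an analysis of variance could supply, gives nearly the same as the one-contrast column: 30% to 18% for seven scales and 23% to 15% for five.

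**Step 4. After the fix.** One endpoint and one lead contrast at two-sided 5%, with later contrasts tested only if the preceding one succeeds, hold the familywise error at 5%.

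**The case against.** The document states no success rule. It does not say that a win on any scale is enough, and it does not say that all must succeed. It gives no alpha, and a multiplicity adjustment may well sit in an analysis plan that is not shown, so its absence from a condensed article is no fault. Statistical methods can be read as one three-group test per outcome, and the stated main aim already points toward multidomain versus non-contact. All of this stands. The percentages in the working are therefore conditional.

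Three stronger readings are tempting, and the documents do not support them.

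- **That there are thirteen co-primary endpoints.** A reader might add seven scales and six sequences. But sequences are not endpoints, and one measure per sequence would be an invention. Co-primary, in its usual sense, means that all must succeed, which costs power and does not inflate type I error.
- **That the protocol counts significance on any scale in any contrast as success.** No sentence says so.
- **That a chance positive trial is likely.** For one contrast the conditional figures lie between 15% and 30%. They stay below one half even with two contrasts, and they presuppose that nothing is adjusted.

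The objection does not reach the contradiction itself. An analysis plan can adjust only within a defined family, and whichever rank it gave imaging would conflict with either the Outcomes paragraph or the Primary outcomes list. Condensing a protocol into an article may drop detail, but it does not explain two different ranks for the same item.

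**Conclusion.** The concern holds as an inconsistency in how the protocol fixes its primary outcome. The opening Outcomes paragraph, Primary outcomes, Secondary outcomes and Table 4 cannot all be followed. As a result, no outcome and no contrast is identified as confirmatory. This rests on the text alone and needs no assumption.

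The size is illustrative. If the scales were tested unadjusted at 5% with any win accepted, the false-positive risk in one contrast would be three to six times the nominal level across the range examined (15/5 = 3 to 30/5 = 6), and more with two contrasts. The assumed level, correlation and success rule are not in the document. The point should be settled before outcome data are analyzed, because it decides what the trial can claim.

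**What to change.** In Outcomes, Primary outcomes and Secondary outcomes:

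1. Name one primary endpoint that Table 4 collects at enrollment and exit. MoCA total score at 6 months is one suitable choice. Another scale, or a defined composite of scales in Table 4, would also serve, provided that one is chosen.
2. Name one primary contrast at two-sided 5%: multidomain versus non-contact, which matches the main aim in Explanation for choice of comparators. If it is significant, test multidomain versus health education, then health education versus non-contact, in that fixed order.
3. Move the remaining scales and all MRI to secondary, as the Outcomes paragraph already says for imaging. Name the derived MRI measures, and list each modality once.
4. Reconcile SCD-Q9 and SCS with Table 4: either add them to the assessments or remove them from the outcome list.

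The cost is mainly wording. The endpoint, contrast and imaging changes use data that Table 4 already plans to collect; only adding SCD-Q9 and SCS to the assessments would mean extra data collection. The real price is that the other scales and imaging can no longer support a primary claim.
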